### Data analysis

A total of 600 patients were randomized to the BI/RT or BI/RT+ conditions, and we stratified based on site, behavioral health consultant, and drug or alcohol severity (mild, moderate, or severe based on AUDIT or DAST-10 score). These stratification variables were chosen to account for possible differences in intervention delivery and treatment response. Specifically, we aimed to account for general site differences such as neighborhood/population served, typical amount of clinical contact received by patients, and range of services available. Similarly, we chose to stratify randomization by BHC in order to equalize non-specific provider variables across conditions. Because severity of substance use has consistently been demonstrated to moderate the impact of brief intervention on substance use [13], we equalized the proportion of mild, moderate, and severe substance use across conditions. Prior to performing all analyses, standard data screening/cleaning procedures will be applied. These procedures will (1) re-screen the data for data-entry errors, (2) check for outliers, (3) assess the extent and pattern of missing data, and (4) check that appropriate assumptions of normality are met and employ remedial measures such as power transformations whenever necessary. The randomization will be checked by comparing the groups on relevant background variables and on all baseline dependent measures. The comparisons will use analyses of variance for continuous variables and log-linear models for discrete or ordinal responses. Some covariates will be considered for inclusion in the main analyses to improve the precision of our hypothesis testing [56]. In addition, we have powered the study sufficiently to conduct subgroup analyses. Based on the literature, it is possible that patients who are using harder illicit drugs (cocaine, heroin, etc.) may respond differently to BI/RT and BI/RT+ than patients who are only using marijuana, or who use marijuana but primarily have a problem with alcohol. We will be adequately powered to break out these subgroups for secondary analysis. Below we specify each hypothesis and discuss the statistical procedures we will employ in analyzing the data.

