#### **Primary H1**

Patients assigned to BI/RT+ will attend more substance intervention and community-based specialty treatment sessions outside of the FQHC over the 12-month follow-up than patients assigned to BI/RT.

A linear mixed effects model [57] will be used to compare participants in the two groups on the number of sessions attended in the past 90 days at the 3-, 6-, 9-, and 12-months follow-up assessments. The model will include terms for intervention group, drug type (i.e., illicit drug or alcohol/marijuana), time, BHC/site, and relevant interactions along with any necessary covariates. For these analyses we will combine alcohol and marijuana use given the high prevalence of co-occurring use as well as the social acceptability and decriminalized status of marijuana in Philadelphia, which can contribute to a decreased perception for need for treatment. Specific contrasts will compare (1) differences between individuals in the illicit drug sub-group who received the BI/RT intervention and those who received the BI/RT+ intervention and (2) differences between individuals in the alcohol/marijuana sub-group who received the BI/RT intervention and those who received the BI/RT+ intervention. The mixed effects model will be performed using SAS’s PROC MIXED.

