Given the mixed results in the current SBIRT literature, this study will also further our understanding of SBIRT’s effectiveness. The results of this study will help shed light on when SBIRT works, for whom, and what intensity is most appropriate for various substances and severities. For example, we may find that BI/RT works well for patients using some substances, but patients using other substances may respond better to the BI/RT+ level of care. Our subgroup analyses will examine whether patients who are using harder illicit drugs (cocaine, heroin, etc.) respond differently to BI/RT and BI/RT+ than patients who are primarily using marijuana or alcohol. We will examine a range of outcomes that are important to patients including substance use, engagement in treatment, and medical and psychosocial functioning. These results will further our understanding of SBIRT’s applications and limitations. Additionally, a strength of this study is that it was conducted in FQHCs with a primarily low-income, Black/African American patient population. Thus this study will provide important information about the effectiveness of these interventions for a traditionally underserved population.

While this study will advance our knowledge about SBIRT, there are a few important limitations to note. First, we did not include a no-treatment control condition where patients receive screening only with no brief intervention. A no-treatment control condition would demonstrate the comparative effectiveness of BI/RT and BI/RT+ and provide a more certain estimate of the true effectiveness of the two brief interventions. We chose not to include a no-treatment condition for ethical reasons. We consider it unethical to identify a patient’s substance use problem and then not provide any services to address the problem. However, this research will enable our team to answer the question of whether providing a BHC the latitude to conduct expanded brief intervention (BI/RT+) at the primary care location yields significantly improved patient outcomes.

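### Severity, a randomisation stratum chosen because it moderates response, is not committed to the H1, H2 and H4 models; name it as a fixed term

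*Protocol article*

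**What the plan says.** **Randomisation.** Under Data analysis the article states that "we stratified based on site, behavioral health consultant, and drug or alcohol severity", with severity in three classes (mild, moderate, severe) taken from the AUDIT or DAST-10 score. The reason given for this stratum is that "severity of substance use has consistently been demonstrated to moderate the impact of brief intervention on substance use".

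**Models.** The Primary H1 section lists the terms: "The model will include terms for intervention group, drug type (i.e., illicit drug or alcohol/marijuana), time, BHC/site, and relevant interactions". The sentence then continues "and relevant interactions along with any necessary covariates". H2 and H4 use models similar to H1 with the baseline response added. Every stated contrast compares the arms within the two drug-type sub-groups.

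**Covariates in general.** Data analysis adds: "Some covariates will be considered for inclusion in the main analyses to improve the precision of our hypothesis testing". None is named.

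**Interpretation.** The Discussion expects the results to show "what intensity is most appropriate for various substances and severities".

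**The concern.** The printed term list carries BHC/site from the randomisation into the analysis but not severity, the one stratum justified by a claim of consistent moderation. Whether it enters a primary model is left to a later judgement of what counts as necessary.

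A stratum that predicts outcome usually belongs in the model for two reasons. It removes explained variance. It also lets the standard error reflect the balance that the design imposed; without it, the reported standard error of a linear model tends to be too large.

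H1 is the most exposed outcome. Its model has no stated baseline covariate. Its outcome, sessions outside the health center, is tied to severity through the referral rules in the BI/RT and BI/RT+ sections. Those rules differ by severity class and, for the moderate class, between arms. That makes it plausible that severity predicts the outcome and that the arm contrast varies with it, but it gives no figure.

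Separately, no stated contrast or named interaction supports the severity part of the Discussion sentence.

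**Working it through.** **1. Inputs from the article.** Two-sided alpha .0125, correlation .5 between repeated measures, 20% attrition, and 100 and 200 per condition in the illicit-drug and alcohol/marijuana sub-groups (Power for the primary hypotheses). Four follow-ups (Patient follow-up procedures). Six BHCs (Methods/design). The share of outcome variance explained by severity, R², is not given. I assume 0 to .20 of the variance of the patient's mean outcome left after the other model terms.

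**2. The stated power reproduces.** The variance factor for the mean of four visits is (1 + 3 × .5)/4 = .625. The detectable d at 80% power is (2.498 + 0.842) × √(2 × .625/n).
- Alcohol/marijuana: d = .264 at n = 200 and .295 at n = 160 (after attrition), inside the stated .25–.30.
- Illicit drug: d = .373 at n = 100 and .417 at n = 80, so the stated .5 is conservative.

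No covariate is needed to reach 80%.

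**3. Precision gained by adding severity.** The model standard error shrinks by about 1 − √(1 − R²): 2.5% at R² = .05, 5.1% at .10 and 10.6% at .20. At the effect giving 80% power without it, adjusted power is Φ(3.339/√(1 − R²) − 2.498) = 82%, 85% and 89%. If R² is instead read as a share of single-visit variance, the ratio of standard errors is √(.625/(.625 − R²)) = 1.04, 1.09 and 1.21.

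**4. How far the unadjusted standard error is overstated.** With severity exactly balanced within the comparison, the overstatement is 1/√(1 − R²) − 1 = 2.6%, 5.4% and 11.8%. The planned contrasts lie within drug type, which is not a listed stratum, so severity is only partly balanced there.

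I simulated 6,000 allocations of 600 patients. Assumptions: blocks of four within 6 × 3 = 18 BHC-by-severity cells, equal severity classes, drug type split 1/3 to 2/3 and independent of severity, 20% random loss. The model held drug type, arm within drug type, and BHC. For each allocation, v is the contrast's diagonal element of (X′X)⁻¹. Regressing the standardised severity score on X gives c, the contrast's coefficient, and f, the residual variance. Then:
- model SE = √{[(1 − R²) + R²f]v}
- true variance = (1 − R²)E[v] + R²Var(c)

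| R² | SE smaller with severity | SE overstated, alcohol/marijuana | SE overstated, illicit drug |
|---|---|---|---|
| 0 | 0 | 0 | 0 |
| .05 | 2.4% | 1.3% | 0.6% |
| .10 | 5.0% | 2.7% | 1.2% |
| .20 | 10.5% | 5.5% | 2.5% |

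At R² = .20 the actual type I error is about .008 (alcohol/marijuana) and .0105 (illicit drug), against .0125. With no attrition, the overstatement at R² = .20 is about 7% and 3.5%.

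**5. A reading by severity.** If the classes were equal thirds (assumption), the same formula gives detectable effects within one class of d = .42 in the whole sample (80 completers per arm), .51 in alcohol/marijuana (53 per arm) and .72 in illicit drug (27 per arm).

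**The case against.** The strongest reply is that this is a journal article whose analysis plan is not shown. The H1 sentence admits further covariates, and Data analysis says some will be considered for precision, which is exactly what is at issue. That stands against any claim that severity is excluded. It does not remove the point: the article prints the model terms, names BHC/site, and commits to nothing for the remaining stratum.

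A reader might infer more than the text supports.

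- **That standard errors are too large by the full exact-balance amount (up to 11.8%).** The primary contrasts are within drug type, where balance is only partial.
- **That the trial is underpowered.** The 80% is reached without covariates. Adjustment is a gain on top, and the error from omission is conservative.
- **That moderation implies prognosis.** The article claims that severity modifies the intervention effect. The precision argument needs it to predict outcome, which is plausible but not quantified.
- **That the same holds for every outcome.** H2 and H4 adjust for the baseline response, which probably absorbs part of severity. For the urine GEE the link is not stated. With a logit link, omission mainly pulls the odds ratio towards the null, and adjustment need not shrink its standard error.
- **That a reading by severity is impossible.** Severity is known for every randomised patient and the H1 sentence leaves interactions open, so the analysis is unspecified. Severity appears in none of H1 to H4, and the Discussion's own examples are by substance.

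**Conclusion.** The point holds in a limited form. Severity is a randomisation stratum that the H1, H2 and H4 models do not commit to, although BHC/site is named. If severity is prognostic, the linear mixed models give up some precision: a model standard error about 2–11% larger than needed for an assumed R² of .05 to .20. The tests are mildly conservative, with the unadjusted standard error overstated by roughly 0–5% in the drug-type contrasts. Those figures rest on the assumed R², block size, equal severity classes, independence of drug type and severity, and 20% random loss. The loss is nil at R² = 0 and likely largest for H1. Nothing here biases the comparison in the linear models or raises the false-positive rate. The Discussion's reference to severities has no specified analysis behind it.

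**What to change.** In Primary H1, and by reference in H2 and H4, name the three-level severity class as entered at randomisation as a fixed term, alongside BHC/site, drug type and time. The cost is one sentence and two degrees of freedom; the variable already exists because it was used to allocate patients.

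For the Discussion statement, choose one of two courses. Either prespecify arm-by-severity as a secondary, exploratory estimate with a confidence interval (two further degrees of freedom), noting that the effects within each class will be imprecise, or remove the reference to severities.

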#### **Primary H2**

Patients assigned to BI/RT+ will demonstrate larger reductions in drug use by point prevalence urine samples and by reported days using over the 12-month follow-up compared to patients in BI/RT.

A generalized estimating equations (GEE) model [58] will be used to compare participants in the two groups on rate of urine-confirmed drug abstinence at each follow-up assessment, and linear mixed effects models will be used to examine days of self-reported drug use in the past 30 days at each follow-up assessment. The models will be similar to those outlined for H1, and the baseline response variable (i.e., urine result or days drug use) will be entered as a covariate in the model. As with H1, contrasts will examine the effects of the intervention separately for the two drug type sub-groups. Analyses will be performed using SAS’s PROC GENMOD (GEE) and PROC MIXED.

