### **H2**

Patients assigned to BI/RT+ will demonstrate larger reductions in drug and alcohol use by point prevalence urine samples and by reported days using over the 12-month follow-up compared to patients assigned to BI/RT.

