### Subject population and setting

A total of 10,935 patients were screened, and 600 eligible individuals were recruited to participate. All participants were patients at three primary care clinics in the Philadelphia metro area. The three clinics in this study are all FQHCs serving traditionally underserved populations, including many low-income and uninsured patients. In addition to providing primary care, the FQHCs offer supportive services such as case management, health education, and prevention using an interdisciplinary approach. The study primarily included adults over the age of 21, but older adolescents (i.e., 18–21 years) were not excluded. All three of the FQHCs are located in neighborhoods of Philadelphia that have greater minority representation than is found for the city as a whole. Our sample was approximately 82 % Black, 7 % White, and 12 % other races. About 8 % were Hispanic and approximately 45 % of our participants were women; the average age was 40. About 30 % were employed either full-time or part-time, 66 % were never married, 11 % were married or cohabitating, and 75 % had at least a high school diploma or equivalent. There was a fairly even split of primary substance use; 35 % of participants primarily used alcohol, 38 % marijuana, and 27 % other substances.

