#### Outcome measures

Primary endpoints of substance use will be measured using an abbreviated version of the *Addiction Severity Index-6th Edition (ASI6)* [50, 51] and urinalyses. The ASI is a multi-dimensional interview used to measure problem severity of substance use, health, and social problems. We used an abbreviated version of the ASI6 that takes approximately 20 min to complete.

*Urinalysis* Urine analyses were conducted using an 8-panel screen that covers the most commonly abused illicit drugs, including marijuana, cocaine, amphetamine, methamphetamine, morphine/opiates, benzodiazepines, barbiturates, and PCP.

*Non*-*Study Medical and Other Services (NSMOS)* The NSMOS was specifically developed for this study and records the number of additional community and specialty care treatment services that patients received for medical, psychiatric, and drug and alcohol needs. The NSMOS also assesses whether the patient received these services in outpatient or acute care settings.

*Severity past year: MINI Plus 5.0.0* The MINI is a short, structured diagnostic interview for DSM-IV and ICD-10 psychiatric disorders [52, 53].

*Chronic Conditions Questionnaire* The Chronic Conditions Questionnaire assesses how well patients manage chronic diseases or conditions.

*Healthy Days Symptoms* The Healthy Days Symptoms measures the number of days over the past month that a patient was affected by symptoms such as pain and anxiety, as well as the number of healthy days.

*Perceived Stress Scale 4*-*Item Version (PSS-4)* The PSS is a global measure of the perception of stress, and has been shown to be correlated with quitting smoking and other measures of health behaviors [54].

*Personal Rulers* The Personal Rulers measure a patient’s perception of importance, readiness, and confidence in reducing or quitting their drug and/or alcohol use.

*HIV Risk Assessment (HIV-RA)* The HIV Risk Assessment provides a brief self-report measure of HIV testing history and sexual risk.

*Client Satisfaction* A Client Satisfaction Form was administered to participants at the 3-month follow-up to assess participant satisfaction and perceived usefulness of the interventions.

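### Primary H2 covers drug and alcohol use, but its analysis and the alpha split name drug outcomes only, so reduced drinking is not tested and alcohol-only participants dilute the alcohol/marijuana contrast

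*Protocol article*

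**What the plan says.** In the aims, H2 predicts "larger reductions in drug and alcohol use by point prevalence urine samples and by reported days using over the 12-month follow-up". The abstract likewise gives days of substance use, not of drug use, as a primary outcome.

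The Primary H2 paragraph under Data analysis restates the hypothesis without alcohol: "larger reductions in drug use by point prevalence urine samples and by reported days using". It then fixes two responses. The binary one is the "rate of urine-confirmed drug abstinence at each follow-up assessment", analysed by GEE. For the continuous one, "linear mixed effects models will be used to examine days of self-reported drug use in the past 30 days at each follow-up assessment". The adjustment is also drug-only: "the baseline response variable (i.e., urine result or days drug use) will be entered as a covariate in the model". As with H1, contrasts are made separately in the illicit-drug and alcohol/marijuana sub-groups.

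The power section divides .05 by four outcomes: treatment sessions, urinalysis-confirmed abstinence, days of self-reported drug use, and acute-care cost. None concerns drinking.

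Under Outcome measures, the urine screen is an 8-panel test "including marijuana, cocaine, amphetamine, methamphetamine, morphine/opiates, benzodiazepines, barbiturates, and PCP". Secondary H4 uses the ASI Medical, Employment, Legal and Psychiatric scores and an HIV risk score.

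On the population, Table 1 makes AUDIT ≥ 8 an entry route of its own. The sample description reports that 35% "primarily used alcohol, 38 % marijuana, and 27 % other substances".

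**The concern.** A primary hypothesis and its analysis name different outcomes. If the analysis paragraph is followed, the alcohol half of H2 has no response variable. If the hypothesis is followed, an alcohol outcome must be chosen that the analysis paragraph does not define and the alpha split does not count. An analyst could defend either course, and the choice could be made after the data are seen.

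The literal reading also affects the estimate. Participants who drink but use no drugs stay in the H2 models through the alcohol/marijuana contrast. In both arms they have negative drug urines and zero drug-use days, whatever happens to their drinking, which pulls that contrast toward zero. H1 includes these participants, but it measures sessions attended, not use.

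**Working it through.** **1. The plan's own figure.** Inputs from the power section: two-sided alpha .05/4 = .0125, correlation .5, 20% attrition, 200 per condition in the alcohol/marijuana sub-group, 80% power for d = .25–.30.

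I take the treatment contrast as the average over the four follow-ups. The variance factor is (1 + 3 × .5)/4 = .625, and the detectable effect is

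d = (z(.99375) + z(.80)) × √(2 × .625/n) = (2.498 + .842) × √(1.25/n).

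- n = 200 (no loss): d = .264
- n = 160 (200 × .8): d = .295

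Both lie inside the stated range, so the method reproduces the plan.

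**2. Share of the sub-group that is alcohol-primary.** 35/(35 + 38) = 35/73 = .479, about 48%. In numbers, .35 × 600 = 210 and .38 × 600 = 228 participants.

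**3. Dilution of the days-of-drug-use contrast.** Let q be the share of alcohol-primary participants who also use drugs and so can respond. The document gives no value, so q runs from 0 to 1. Suppose those who can respond have d = .30, the others have zero effect, and the standard deviation is unchanged. Then

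effective d = .30 × [1 − .479 × (1 − q)], power = Φ(effective d/√(1.25/n) − 2.498).

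| q | effective d | power, n = 160 | power, n = 200 |
|---|---|---|---|
| 0 | .156 | 23% | 30% |
| .25 | .192 | 37% | 47% |
| .5 | .228 | 53% | 65% |
| .75 | .264 | 69% | 80% |
| 1 | .300 | 81.5% | 90% |

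The recruited split implies .73 × 600/2 = 219 per condition, or about 175 after 20% attrition, which lies between the two columns. With d = .25 and n = 160, power runs from 15% (q = 0) to 63% (q = 1).

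These figures leave out the baseline covariate, which would recover part of the loss.

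**4. Cost of a fifth outcome.** Alpha becomes .05/5 = .01 and the critical value 2.576. At d = .30 and n = 160, .30/√(1.25/160) = 3.394, so power is Φ(3.394 − 2.576) = 79.3%, against 81.5% at alpha .0125.

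**The case against.** The strongest reply is that the analysis paragraph uses drug loosely. Table 1 lists alcohol under a column headed Drug, the H1 model treats alcohol/marijuana as a level of drug type, and the outcome section speaks of endpoints of substance use measured by the ASI6 and urinalysis. Days of drug use might therefore include drinking days. This is possible, but the Primary H2 paragraph does not say it. Elsewhere the document separates the two terms, as in the aims version of this hypothesis, "larger reductions in drug and alcohol use by point prevalence urine samples and by reported days using". The reading lowers certainty about intent; it does not remove the contradiction.

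A reader might also infer that the 35% whose primary substance is alcohol cannot show any benefit, or that half the sub-group carries no signal. The document does not support that. Primarily using alcohol is not using alcohol only. The H1 paragraph gives frequent co-use as a reason for pooling alcohol with marijuana, and the Data analysis introduction describes patients who use marijuana but whose main problem is alcohol. Such patients can change on both H2 outcomes. The no-effect statement holds only for alcohol-only users, whose number is not reported.

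For the same reason, the 23% is a worst case. It also ignores the planned baseline adjustment: alcohol-only users are predictably negative at baseline and afterwards, so the covariate absorbs some of the dilution.

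Nor does the plan need its urine analysis restricted to drug users at baseline. That analysis would have fewer participants: 160 × 38/73 ≈ 83 per condition if limited to marijuana-primary patients. It would not clearly gain power when co-use is common.

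**Conclusion.** The contradiction stands. As written, the plan cannot answer the alcohol part of primary H2: neither H2 response, neither baseline covariate and none of the four outcomes in the alpha split measures drinking, and H4 does not fill the gap. A third of the sample has alcohol as its primary substance, so the mismatch needs correcting.

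The harm to the alcohol/marijuana contrast is real but of unknown size. The 23% to 81% range for the days-of-use contrast rests on an assumed d = .30 among those able to respond, 160 per condition, correlation .5, an unchanged standard deviation and no baseline adjustment. It turns on a co-use share that the document does not report.

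**What to change.** Bring the abstract, the aims version of H2, the Primary H2 analysis and the power section into agreement:

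- Add ASI6 days of alcohol use in the past 30 days as an H2 response, using the mixed model already planned, with baseline alcohol days as covariate.
- List it among the primary outcomes and restate the split as .05/5 = .01. At d = .30 and 160 per condition this costs about two points of power (81.5% to 79.3%).
- Say explicitly that days of drug use excludes alcohol.

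This needs no new data if the abbreviated ASI6 kept the alcohol-day items. The document does not settle that, so the sponsor should confirm it. If the items were not kept, limit H2 and its conclusions explicitly to drug use.

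A urine-abstinence analysis among participants with drug use at baseline may be added as a sensitivity analysis. It need not replace the planned one. Replacing the self-report outcome by a composite of alcohol or drug days, or by days of the primary substance, is a debatable alternative: the composite can hide a fall in drinking among daily marijuana users, and the other changes the estimand.
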